#### Questionnaires

Self-management behavior will be evaluated by the Summary of Diabetes Self Care Activities (SDSCA). SDSCA is an 11-item brief self-report questionnaire for measuring levels of T2DM self-management behaviors with diet (5 items), exercise (2 items), blood sugar testing (2 items), and foot care( 2 items) in last 7 days, which has great reliability and validity for both research and practice [68].

Dietary intake will be assessed by self-administered diabetes eating behavior questionnaire, including sugar and fat (5 items), fruit and vegetable (5 items), oil and salt eating habits (4 items), cooking and dining habits (4 items), and dietary monitoring behavior (4 items).

Physical activity during the last 7 days will be assessed by International Physical Activity Questionnaire Short Form (IPAQ-SF), including items for time spent on slight, moderate, vigorous activities or sedentary behavior [69].

Medication taking behavior will be evaluated by the Adherence to Refills and Medications Scale (ARMS) [70], a 12-item scale containing taking medications as prescribed and refilling medications on schedule, which has great validity and reliability for measuring medication adherence.

Emotional state will be measured by the 7-item Generalized Anxiety Disorder (GAD-7) [71], the Patient Health Questionnaire 9 (PHQ9) [72], and the 4-item Perceived Stress Scale (PSS-4) [73], which reflect participants’ levels of anxiety, depression, and stress over the last two weeks.

Health literacy will be evaluated by 12-item short-form health literacy scale (HLS-SF12) [74], which includes 12 dimensions of health literacy with 12 questions about finding, understanding, judging, and applying health information about disease management, prevention, and health promotion.

Diabetes self-management skills will be assessed by a self-designed 9-item scale for people with T2DM, including determining if their weight is normal, calculating their daily calorie needs, designing personalized recipes, determining the size of the effect of regular food on blood sugar, adjusting their diet according to the amount of exercise they do, developing their own exercise plan, judging the intensity of various exercises, and knowing how to avoid and deal with hypoglycemia.

Self-efficacy will be measured by self-designed diabetes self-management scale, which reflects the confidence to do diabetes self-management behaviors, including diet (5 items), physical activity (7 items), identify and manage hypoglycemia (2 items) and access medical services (2 items).

Change of self-management behaviors will be evaluated by a self-designed 31-item MTM scale for health behavior change, including participatory dialogue, behavioral confidence, changes in the physical environment and social environment, emotional change, and behavioral change.

Quality of life will be measured by five-level EuroQol five-dimensional questionnaire (EQ-5D-5L) [75], which comprises five dimensions about mobility, self-care, usual activities, pain/discomfort, and anxiety/depression.

Cloud data: The cloud data from the AI-HEALS will be used to evaluate users' FAQRobot interaction records and reading behavior data on a weekly basis. The FAQRobot interaction records include user ID, user questions, bot answers, human–computer interaction time (accurate to the second) and outgoing talk module (knowledge reasoning engine, and common standard questions). User reading behavior data includes article clicks and reads, reading time per article, average effective reading rate (patients/articles), follow rate and unfollow rate of the WeChat service platform "PKU Diabetes Butler", and article Retweets. A collaboration agreement for this project has been made with the Emotibot company. The data will not include users' personal information, and will be used exclusively for this project and cannot be used for other purposes without authorization.

### Economic evaluation

To assess the efficacy of this mHealth education program on health equality, the economic evaluation will be reported as ICERs and compared between the AI-HEALS-based intervention and traditional T2DM primary care. During the trial, the economic cost of healthcare utilization (medical consultations, use of outpatient, hospitalized, and primary care services, medicine expenditures, accident visits, and lost productivity) will be assessed per case, as well as the cost of project implementation (AI-HEALS-based interventions (plus primary usual care activities) versus primary usual care activities). Utility will be evaluated in terms of HRQoL, with data from the EQ-5D-5L used to calculate health utility values.

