
In summary, given the great potential of patient-oriented KBQA technology for diabetes prevention and control in primary healthcare, the primary goal of this study is to develop a personalized, sustainable and cost-effective health education intervention program, AI-HEALS, to improve the outcome and self-management skills of people with T2DM.

The specific objectives are:1. Evaluate the impact of the AI-HEALS-based intervention program on blood glucose control of T2DM patients.2. Determine the efficacy of the AI-HEALS-based intervention program in improving self-management abilities among T2DM people:2.1 The effectiveness of a healthy diet;2.2 The effectiveness of moderate PA;2.3 The effectiveness of regular medication administration;2.4 The effectiveness of regular blood glucose monitoring.3. Compare the acceptability and cost-effectiveness of AI-HEALS-based intervention program in T2DM primary healthcare.

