#### Intervention arm: SDPC plus AI-HEALS-based T2DM online health education program

Participants will receive SDPC plus AI-HEALS-based intervention through the WeChat service platform "PKU Diabetes Butler" on their mobile phones, which consists of four components:1. KBQA for T2DM knowledge. Participants will be encouraged to interact with a FAQRobot (Frequently Asked Questions Robot) to accurately and efficiently gain detailed knowledge about T2DM diet (recommended or not recommended foods, food nutrients, calories, glycemic index, and glycemic load), exercise (recommended or not recommended exercise, the metabolic equivalent of physical activities), and medication management (types of medicines and how to take them), removing time and distance limitations to health care consultations and increasing health care accessibility. In addition, the FAQRobot has an entertainment function, which can tell jokes and play games with patients to calm them down. After reviewing guidelines, professional literature, and consulting experts, we identified the source material and knowledge for the T2DM self-management KQBA. Subsequently, we uploaded the underlying data to the Bot Factory^22^ Dialogue AI Platform produced by Emotibot [67], which formed an automated Q&A bot with semantic understanding and automatic knowledge mining. The Q&A bot was linked to the WeChat platform "PKU Diabetes Butler". The backend stores the questions that participants asked as well as their usage behaviors (such as time and frequency) so that we can improve the knowledge graph regularly and assess the usage patterns of participants.2. Recording and monitoring of physiological indicators as well as lifestyle behaviors. Participants will be encouraged to record information on physiological indicators (blood glucose, blood pressure), diet, physical activity, and medication-taking regularly on the platform, which stores and uploads the records electronically and enables long-term monitoring of blood glucose control and changes in self-management behaviors.3. A reminder service for taking medications and monitoring blood glucose levels. Participants will be encouraged to enter the time they want to be reminded in the system, and the platform can remind them to take their medication or monitor blood glucose levels at specified time.4. Automated and personalized messaging about diabetes self-management. Participants will receive 1–3 automated messages about T2DM control and management per week, the content of which will be based on multi-theory model (MTM) of health behavior change, and will contain knowledge of T2DM diet, exercise, and medication taking to increase health literacy and to encourage behavioral change. Furthermore, based on the questions users ask the FAQRobot, the system will accurately push additional, tailored articles. Researchers will also regularly log into the backend to check the number, type and time of articles read by the participants in order to tailor the content and frequency of messages to their reading patterns.

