### Outcomes

Primary outcome: Change of HbA1c from baseline to 1, 3, 6, 12, and 18-month follow-up.

Secondary outcomes:1. Modifications of self-management behaviors: dietary, physical activity, blood glucose monitoring, and medication adherence.2. Social cognition and psychology: diabetes health literacy, self-efficacy, depression, anxiety and stress.3. Metabolic control: self-reported fasting plasma glucose or 2 h plasma glucose, dose of insulin and medicine, other indicators such as blood pressure, blood lipids, and BMI.4. Economic evaluation: A comparison of incremental cost-effectiveness ratios (ICERs) will be conducted between the AI-HEALS-based intervention and usual care of T2DM. Therefore, health-related quality of life (HRQoL), healthcare utilization, including medical consultations, use of healthcare (outpatient, hospitalized, and primary care services), medicine purchases, accident visits, and direct non-medical costs (diabetes-related transportation, lodging) will be collected.

Additionally, the rate of recruitment and drop-out, as well as the reasons for drop-out, will be gathered. To determine whether the data is homogeneous, demographic characteristics and study outcomes will be compared between people dropping out and participants resistant to the entire trial during data analysis.

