### Variables measurement

Sociodemographic variables will be obtained at baseline. Physical examinations and questionnaire surveys will be completed at baseline, 1, 3, 6, 12, and 18 months (Table 1).

**Table 1 Tab1:** Data collection components and collection timeline

Type of research	Data collection component		Timepoint					
			0 M	1 M	3 M	6 M	12 M	18 M
Quantitative research	Sociodemographic variables	sex, age, marital status, location, family average household, educational level, occupation, clinical information	√					
	Blood glucose	HbA1c levels	√		√	√	√	√
	Anthropometric variables	height, weight, waist circumference, and blood pressure	√	√	√	√	√	√
	Self-management behavior	Questionnaire: SDSCA	√	√	√	√	√	√
	Dietary intake	Questionnaire: self-administered diabetes eating behavior questionnaire	√	√	√	√	√	√
	PA	Questionnaire: IPAQ-SF	√	√	√	√	√	√
	Medication taking	Questionnaire: ARMS	√	√	√	√	√	√
	Emotional stage	Questionnaire: GAD-7, PHQ9, and PSS-4	√	√	√	√	√	√
	T2DM knowledge and skills	Questionnaire: HLS-SF12 and self-designed 9-item diabetes self-management skills scale	√	√	√	√	√	√
	Self-efficacy	Questionnaire: self-designed diabetes self-management scale	√	√	√	√	√	√
	Behavioral change	Questionnaire: self-designed 31-item MTM scale for health behavior change	√	√	√	√	√	√
	Quality of life	Questionnaire: EQ-5D-5L	√	√	√	√	√	√
	Economic evaluation	healthcare utilization (medical consultations, use of outpatient, hospitalized, and primary care services, medicine expenditures, accident visits, and lost productivity)					√	√
	Cloud data	KQBA interaction records and user reading behavior data		√	√	√	√	√
Qualitative research	Person-in-depth semistructured interview	User experience of the AI-HEALS		√	√	√	√	√

Sociodemographic variables: sex, age, marital status, location, family average household, educational level, and occupation will be gathered, as well as clinical information such as the duration of T2DM, detailed medical history, and current diabetes medications.

Measurement of blood glucose: HbA1c levels will be measured by drawing venous blood fasting.

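### No cost list names glucose self-monitoring supplies, whose use AI-HEALS aims to increase; if monitoring rises and they are not captured elsewhere, the ICER leans in its favour

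*Protocol article*

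**What the plan says.** The Protocol article itemises costs in three places.

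- Outcomes, secondary outcome 4: consultations and use of care, followed by "medicine purchases, accident visits, and direct non-medical costs (diabetes-related transportation, lodging) will be collected". The list is introduced by the word *including*.
- Variables measurement, Table 1, economic row: consultations and use of care, then "medicine expenditures, accident visits, and lost productivity", collected at 12 and 18 months.
- Economic evaluation: "medical consultations, use of outpatient, hospitalized, and primary care services, medicine expenditures, accident visits, and lost productivity) will be assessed per case". This section adds programme cost ("as well as the cost of project implementation") without breaking it down, and takes utility from the EQ-5D-5L.

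The Intervention section gives the AI-HEALS arm two features that bear on glucose testing. Component 2 reads: "Participants will be encouraged to record information on physiological indicators (blood glucose, blood pressure), diet, physical activity, and medication-taking regularly". Component 3 is described as "A reminder service for taking medications and monitoring blood glucose levels". The control arm receives standard primary care without either. Specific objective 2.4 in the Background is "The effectiveness of regular blood glucose monitoring", and glucose monitoring is among the behaviours in secondary outcome 1.

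**The concern.** A cost-effectiveness comparison should count the resources that the intervention is designed to change. Component 3 targets two behaviours, taking medicines and checking glucose. The cost of the first is named in all three lists; the cost of the second is named in none. Any quality-of-life gain from better monitoring would still enter the ICER through the EQ-5D-5L. Followed as written, the plan could credit the benefit of extra testing and leave out what the testing costs.

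The gap would not cancel between arms, because only one arm is prompted. It would also grow with success on objective 2.4. The cost-effectiveness half of objective 3 relies on this ratio.

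**Working it through.** The article gives no cost, ICER, test frequency or supply price, so there is no figure of its own to reproduce. The check has two parts: comparing the lists, then bounding the possible error.

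**1. The lists side by side**

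| Item | Outcomes, no. 4 | Table 1 | Economic evaluation |
|---|---|---|---|
| Consultations | yes | yes | yes |
| Outpatient, hospital, primary care | yes | yes | yes |
| Medicines | yes | yes | yes |
| Accident visits | yes | yes | yes |
| Transport and lodging | yes | no | no |
| Lost productivity | no | yes | yes |
| Implementation cost | no | no | yes, not itemised |
| Glucose-monitoring supplies | no | no | no |

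The omission is common to all three. Patient-borne costs are in scope, since medicine purchases, transport and lodging are counted in one list and lost productivity in the other two.

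**2. Direction of the error**

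Let m be the supply cost per patient that arises in the intervention arm beyond the control arm and is recorded nowhere. With ΔC the true cost difference and ΔE the QALY difference, the reported ratio is (ΔC − m)/ΔE. For ΔE > 0 it is too low by m/ΔE. The direction favours AI-HEALS whenever m > 0. If monitoring does not rise, or supplies are captured elsewhere, m = 0 and there is no error.

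**3. Size, on assumed inputs**

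m = extra tests per week × price per test × weeks.

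The tests and prices are assumptions. The weeks run from the 3-month intervention (13 weeks) to the 18-month follow-up (18 × 52/12 = 78 weeks).

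- Low end: 1 × 1 CNY × 13 = 13 CNY per patient.
- Middle, intervention period only: 3 × 2 CNY × 13 = 78 CNY.
- Middle, habit lasting the whole follow-up: 3 × 2 CNY × 78 = 468 CNY.
- High end: 7 × 4 CNY × 78 = 2,184 CNY.

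The high end is 2,184/13 = 168 times the low end.

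**4. Effect on the ratio**

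This needs a further assumption, the QALY gain. For 0.005 to 0.02 QALY, the shift runs from 13/0.02 = 650 to 2,184/0.005 = 436,800 CNY per QALY. That range is too wide to say whether the omission matters in practice, and nothing below rests on it.

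**The case against.** The strongest reply is that this is a journal article, and the line items of a resource-use questionnaire are commonly left to fuller documents. Nothing in the text says supplies are excluded. The list under Outcomes is openly illustrative, and the three lists disagree on transport, lodging and lost productivity, which suggests summaries. *Medicine purchases* and *medicine expenditures* are not defined and could include pharmacy-bought strips; implementation cost is not itemised; the article does not say who pays for supplies or from which perspective costs are counted. The reminders also depend on participants choosing to set a time, so a rise in testing is not assured.

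Much of this stands, and it limits the point. A reader might infer that the intervention arm will look too cheap and that the ICER is biased as a matter of fact. The document does not support that: whether testing rises is itself a trial outcome, and supplies may be recorded under another heading. Nor is testing the only patient cost the programme could raise; medication is prompted by the same component, and its cost is counted.

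The appeal to condensation does not dispose of the point. The article states its cost items three times, down to accident visits and lodging, and two of the lists are written as complete parentheses. A resource that the programme itself targets is absent from each. In ordinary usage meters and lancets are not medicines, so without a definition respondents and coders may classify them differently.

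**Conclusion.** The point holds in conditional form. The stated cost items omit self-monitoring supplies, although the programme seeks to increase monitoring in one arm only. The incremental cost is understated, and the ICER leans towards AI-HEALS, if two things are true: monitoring rises more in the intervention arm, and the supplies are not captured under medicines or implementation cost. The point also assumes that these purchases fall within the costing perspective, which the patient-borne items already listed make reasonable.

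The size cannot be determined from the document. The 13 to 2,184 CNY per patient range is illustrative, and its top end assumes a daily extra test sustained for about 15 months after the 3-month intervention ends (18 − 3). The economic evaluation is a secondary outcome; the HbA1c comparison is untouched, as is the acceptability part of objective 3. The change is worth making because it is cheap and the direction of a possible error is foreseeable.

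**What to change.** Add *blood glucose self-monitoring supplies (strips, lancets, meters)* to the cost items under Outcomes, in the economic row of Table 1 and under Economic evaluation. Collect it with one questionnaire item, worded identically in both arms. Alternatively, state that an existing item, such as medicine expenditures, covers these supplies, and word that item so that respondents include them.

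As an optional sensitivity analysis, cost monitoring frequency from the two SDSCA blood sugar testing items at a common unit price. These are planned in both arms at all six time points. The article says only that they cover the last 7 days; they may not count individual tests, so this would be an approximation and not a substitute for the direct item.

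The cost is one more question, one more line in the cost model and possibly a slightly less favourable ICER. The article states that recruitment had not begun, and Table 1 first collects economic data at 12 months, so the item could be added before any of these data are lost.

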### Qualitative analysis

Semistructured interviews of participants will be conducted at 1, 3, 6, 12, and 18 months after the baseline to investigate feedback, including program appeal, acceptability, usability, and participant satisfaction. The interview data will provide us a better understanding of the factors that drive engagement and behavioral changes in participants. We will invite participants to a 40-min telephone-based or face-to-face personal in-depth interview. Participants will be selected considering the sociodemographic variables including sex, age, location, educational level and the duration of T2DM. Topics about personal experience, recommendations for the developments of the AI-HEALS as well as motivating factors and difficulties of maintaining self-management behaviors are all encouraged to be discussed. Participants will be recruited successively until thematic saturation has been reached. Interview audio files will be transcribed verbatim and de-identified, and analysed by NVivo (version 12, QRS International, Doncaster, Australia) using the theoretical domains framework. The qualitative data and quantitative data will be incorporated to better explain the results at multiple stages during the trial.

### Statistical analysis

Data from the quantitative study will be recorded in the designed questionnaire and double-parallelly entered into Epidata 3.1 (Version 15.0.5, Odense, Denmark). Variables analysis will be based on the premise of intention to treat. Continuous variables will be presented as mean ± SD (M(P_25_, P_75_), if they are abnormal distribution), and be compared using Student's t test or one-way ANOVA (or non-parametric tests if necessary). Data distribution will be identified by a Kolmogorov–Smirnov test. Categorical data reported as n(percentage of sample) will be compared using χ2 tests. With regard to the cross-sectional analysis, linear regression, logistic regression and structural equation model (SEM) will be conducted to explore the influence factors of behaviors pattern and mHealth usage pattern evaluated by the group-based trajectory model (GBTM). For longitudinal data, a generalized linear mixed model (GLMM) will be used to identify the effectiveness of the AI and mHealth-based intervention in behavioral changes and diabetic control. Set an alpha risk of 0.05 for two-sided tests. Data will be analysed using IBM SPSS Statistics version 24.0 (SPSS Inc., an IBM Company, Chicago, Illinois, USA), Stata (version 14.0, Stata Corporation, College Station, TX) and M*plus* (version 7.4, Muthén & Muthén, Los Angeles, CA, USA).

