### Study setting and randomization

The study will be conducted in 40-45 community health centers (CHCs) in Beijing, China, as the unit of randomization. The community health center contains 8-10 people with T2DM. A computer-generated list of random numbers will assign clusters (CHCs) in a 1:1 ratio to an intervention group and a control group. All subjects in each cluster will receive the same intervention (SDPC plus AI-HEALS) or control (SDPC). Blinding of the participants or researchers cannot be guaranteed considering the nature of the intervention. The proportion of sociodemographic characteristics (such as gender, age, and location) between two groups will be evaluated at baseline to verify that the data are balanced and comparable. Study designer will generate the allocation sequence, CHCs staff will enroll participants, and study designer will assign participants to interventions.

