### Effect size

Based on our previous study, assuming an alpha risk of 0.05, a beta risk of 0.10, an intraclass correlation (ICC) of 0.002, a mean level of HbA1c in patients with type 2 diabetes of 7.13%, and a standard deviation (SD) of 1.60%, at least 2 clusters, and 166 subjects (138 total before considering a dropout rate of 20%) in each cluster are expected to be recruited according to the sample size formula for unmatched studies [66] to detect a decrease in HbA1c to 6.50% after the intervention. As a result, a total of 664 patients in 4 communities are required to be recruited for this program.

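### Health centres are randomised and an ICC enters the sample size, but no stated analysis accounts for the centre, and tests that assume independent patients are not limited to description

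*Protocol article*

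**What the plan says.** All references are to the protocol article.

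- **Study setting and randomization:** "The study will be conducted in 40-45 community health centers (CHCs) in Beijing, China, as the unit of randomization". Allocation is by cluster: "A computer-generated list of random numbers will assign clusters (CHCs) in a 1:1 ratio to an intervention group and a control group". On cluster size: "The community health center contains 8-10 people with T2DM".
- **Effect size:** the calculation proceeds by "assuming an alpha risk of 0.05, a beta risk of 0.10, an intraclass correlation (ICC) of 0.002". It arrives at 2 clusters of 166 (138 before dropout), for a total of 664 patients in 4 communities.
- **Statistical analysis:** continuous variables are compared by Student's "t test or one-way ANOVA (or non-parametric tests if necessary"), and categorical data "will be compared using χ2 tests". No sentence limits these tests to baseline tables or description. Linear and logistic regression and structural equation models are for cross-sectional exploration of behaviour and usage patterns. For longitudinal data, "a generalized linear mixed model (GLMM) will be used to identify the effectiveness" of the intervention on behaviour and diabetic control. The section names no random effect for CHC or participant, no robust variance and no cluster-level analysis.
- **Study management:** experts are to be consulted on the choice of statistical methods during data analysis.

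**The concern.** In a cluster-randomised trial the comparison between arms has to reflect the unit that was randomised. Patients of one CHC share staff, routines and neighbourhood, so their outcomes are correlated. The t, ANOVA, rank and chi-square tests treat every patient as independent information. A mixed model with only a participant effect would allow for repeated visits but still treat patients of one CHC as unrelated.

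The plan recognises clustering when it sizes the trial and not when it describes the analysis. At stake are confidence intervals that are too narrow and a type I error above 5% for HbA1c and the secondary outcomes. The choice also stays open: with method selection left to consultation during analysis, a clustered and an unclustered result could both be at hand when the decision is made.

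**Working it through.** **Inputs from the protocol.** Two-sided alpha 0.05, power 0.90, ICC 0.002, HbA1c mean 7.13% with SD 1.60%, target 6.50% (difference 0.63), 8-10 patients per CHC in 40-45 CHCs, or 138-166 per cluster in 4 clusters. ICCs of 0.02 and 0.05 are assumptions, used only to show a range.

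**Reproducing the plan's figure.** For independent patients, n per arm = 2(1.960 + 1.282)² × 1.60² / 0.63² = 135.5, so 136. Two routes lead from there to 138:

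- The unmatched-cluster formula c = 1 + f[2σ²/m + k²(μ0² + μ1²)]/δ², with f = (1.960 + 1.282)² and 0.002 entered as the between-cluster coefficient of variation k, gives c = 1.99 clusters per arm at m = 138.
- 136 × [1 + (m − 1) × 0.002] with m = 8 to 10 gives 137.9 to 138.4, but per arm.

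Then 138 × 1.2 = 165.6, so 166, and 4 × 166 = 664. The stated figures reproduce with a clustering term in the calculation.

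**Effect of ignoring the CHC.** Design effect DE = 1 + (m − 1) × ICC. Naive SE divided by correct SE = 1/√DE. True type I error of a nominal 5% test = 2[1 − Φ(1.960/√DE)]. For example, with m = 138: DE = 1 + 137 × 0.002 = 1.274, √DE = 1.129, 1.960/1.129 = 1.736, type I error 0.082.

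| m per cluster | ICC | DE | naive / correct SE | type I error |
|---|---|---|---|---|
| 8 | 0.002 (stated) | 1.014 | 0.993 | 5.2% |
| 10 | 0.002 (stated) | 1.018 | 0.991 | 5.2% |
| 138 | 0.002 (stated) | 1.274 | 0.886 | 8.2% |
| 166 | 0.002 (stated) | 1.330 | 0.867 | 8.9% |
| 8 | 0.02 (assumed) | 1.140 | 0.937 | 6.6% |
| 10 | 0.02 (assumed) | 1.180 | 0.921 | 7.1% |
| 8 | 0.05 (assumed) | 1.350 | 0.861 | 9.2% |
| 10 | 0.05 (assumed) | 1.450 | 0.830 | 10.4% |

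**Degrees of freedom.** A cluster-level comparison has (number of clusters − 2) degrees of freedom.

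- With 4 clusters that is 2, with a critical t of 4.30. At ICC 0.002 and 138 per cluster, SE = 1.60 × √(2 × 1.274/276) = 0.154. Power for 0.63 is then about 58%, or about 63% with 166 per cluster. Treating patients as independent gives more than 99%.
- With 40 CHCs there are 38, with a critical t of 2.02. Power with 8-9 per CHC is about 93-95%, against 94-96% if the CHC is ignored.

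The table uses the normal approximation, so it does not include the loss from having only 2 degrees of freedom.

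**The case against.** The strongest reply is that effectiveness on behaviour and diabetic control is assigned to a mixed model, which can hold a CHC effect. A condensed article commonly leaves random effects, degrees of freedom and covariates to a fuller document that is not shown. The t and chi-square tests appear in sentences on how variables are presented, and the protocol has other uses for them: the baseline balance check and the comparison of drop-outs with completers. The regressions and structural equation models are exploratory.

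Much of this stands. A reader might infer that every named analysis treats patients as independent, or that the mixed model excludes the CHC and its standard errors are wrong. The text supports neither: it gives no random effects at all for that model. The exploratory regressions do not bear on the arm comparison either.

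It is also fair that the primary outcome is change in HbA1c. Stable differences between CHCs cancel in a change, so the ICC that matters is that of the change, which the protocol does not give.

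A reader might also infer that baseline HbA1c has been wrongly left out as a covariate. The section lists no covariates, so that would read silence as exclusion. Against a plain change-score analysis, baseline adjustment multiplies the variance by (1 + r)/2, a 15-25% reduction for an assumed correlation of 0.7-0.5. That is an optional gain, not the repair of an error.

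What the reply does not remove is that the independence-based tests are positively stated with no limit on their use, and that the randomised unit appears nowhere in the described analysis.

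**Conclusion.** The concern holds as a mismatch between randomisation and stated analysis: CHCs are randomised and clustering enters the sample size, but nothing in the analysis section accounts for it. Standard errors that are too small are established for between-arm use of the unadjusted tests whenever the ICC is positive. For the mixed model they are only a possibility that the text leaves open.

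The size is conditional. It is negligible at the stated ICC with 8-10 per CHC (5.2%). It is material with the clusters of the sample-size paragraph (8.2-8.9%, before the 2-degrees-of-freedom problem). At 8-10 per CHC it reaches about 9-10% only if the ICC is 0.05, a value that is not in the protocol. These figures take the ICC to apply to the outcome analysed. The protocol states a single ICC, alongside its HbA1c assumptions, and none for the behavioural outcomes. A small planning value does not justify unclustered tests, because the observed ICC is unknown until the data are in.

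**What to change.** In Statistical analysis, state that:

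1. Every between-arm comparison of HbA1c and of the secondary outcomes uses the planned mixed model, with random effects for CHC and for participant within CHC, and small-sample degrees of freedom (Satterthwaite or Kenward-Roger).
2. Unadjusted t, ANOVA, rank and chi-square tests are used for description only.
3. The observed ICC is reported.

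Reconcile the number and size of clusters between Study setting and randomization (40-45 CHCs of 8-10, so 320-450 patients) and Effect size (4 communities of 166, so 664), because the degrees of freedom depend on them. Baseline HbA1c may be added to the model for precision.

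The cost is wording. Cluster membership is known from the randomisation and a mixed model is already planned. Intervals may be slightly wider where the ICC is not negligible. If 4 clusters is the true design, the correct degrees of freedom will expose low power, but that is a property of the design and not a cost of the analysis.
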